### Intervention

The IM professional practice model for primary care utilizes an inter-professional, physician-led, integrative clinical team to provide patient-centered care. UAIHC services include conventional medical care, lifestyle interventions, and evidence-based CM interventions. In particular, services include longer visits with providers, a commitment to health, a partnership agreement with the health care team, increased access via telephone and email in addition to in-person visits and classes, and a wider range of services including nutritional counseling, acupuncture, chiropractic care, stress-reducing mind-body approaches, and health coaching. In addition to individual appointments, group visits and health promotion classes are offered (e.g., nutrition, yoga, meditation). Emphasis is placed on motivating and supporting lifestyle behavior change. Although patients with a wide variety of diagnoses will be eligible and included in the study, outcomes for patients with the following five conditions (low back pain, fibromyalgia, other musculoskeletal conditions, metabolic syndrome and diabetes, and cardiovascular disease) will be analyzed separately where possible.

The UAIHC business model uses a hybrid financing approach that utilizes usual insurance reimbursements supplemented by a patient membership fee. The membership fee covers a certain number of CM practitioner visits, health coaching visits, and classes (a “class” may comprise a series of individual sessions). Three fee tiers have been established: 1) basic bundle (5 visits with the patient’s choice of CM practitioners, 2 visits with a health coach, and 2 groups or classes); 2) core (10 visits with the CM practitioners of choice, 4 health coach visits, and 4 groups or classes); and, 3) expanded (20 visits with CM practitioners, 8 visits with a health coach, and 8 groups or classes). For some members, this fee is partially offset by collaborating employers who offer UAIHC as an employee health benefit option. (Grant funding supports the costs of this study for those participants employed with these collaborators).

According to its business plan, the IM primary care practice model will follow IM principles [44] as well as the principles of primary care [45,46] and the patient-centered medical home [47]. More detail on the IM primary care practice model is presented in Dodds et al [48].

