### Comparison group(s)

Data from UAIHC patients will be compared, where possible, to those of patients seen in other clinics. The primary outcome, total healthcare utilization, will be obtained from healthcare claims data for patients whose employers have given access to those data. For these patients, matched comparison groups will be developed using two different matching algorithms applied to de-identified claims data for non-UAIHC patients. One will use a straight matching algorithm based on age and gender, and the other will use propensity scores to match [49]. At least one of the participating employers also has employee lab values available. Where these data are available, the same matched comparison groups will be used to compare changes in key lab values seen across groups. Finally, several of the self-report measures have national and regional comparisons available. The measures of patient experiences and patient satisfaction are drawn from the Consumer Assessment of Healthcare Providers and Systems (CAHPS) Adult Visit Survey 2.0 [50]. The CAHPS website contains data on the results of these questions nationally, by region, and by physician specialty. The results seen for UAIHC participants will be compared to those seen by all providers nationally, by all providers in the West region, and by family practice doctors nationally. The measures of diet and exercise quality come from the Center for Disease Control and Prevention’s Behavioral Risk Factor Surveillance System survey [51]. National and statewide averages are available for these items. Unfortunately, no other secondary data sources are available for comparisons. For all other outcomes, UAIHC participants will act as their own controls by comparing their outcome measures over time to baseline.

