### Data Collection

For the outcomes evaluation, data will be collected from patient charts and self-reports at four intervals—baseline (initial clinic visit), and at 3-, 6-, and 12-month follow up periods. Participants will receive a reminder email one week before each data collection due date. Baseline data will be due within one week of enrollment. In the email they will be directed to a secure website where they can access and complete the outcomes data collection instrument. If participants have not entered their data within 3 days of their due date, they will receive another reminder email, and those who have not entered their data within another 3 days of their due date will receive a call from the UA Study Coordinator. Healthcare utilization and cost data from healthcare claims will be obtained from their employer with study participant consent. These data will be collected for one year before and one year after clinic enrollment approximately 3 months after the 12-month follow up period to allow time for all incurred claims to be recorded. De-identified claims data for the comparison groups will be collected for the same period of time with “baseline” being defined by the average start date of study participants.

Because the intervention may change over time as clinic operations start up and mature [21], fidelity monitoring data will be collected monthly from study start for 6 months, then quarterly for 6 months, and then semi-annually. Patient-reported fidelity data will be gathered on a single randomly chosen day of the last week of the data collection month from all patients seen at the UAIHC clinic that day. This day will be selected by the UA research team using a simple computer generated randomization scheme and delivered to the UA Study Coordinator the week before the data collection week. A self-administered patient version of the “How is UAIHC doing?” questionnaire will be used for patients. For clinic personnel, fidelity data will be collected during the last week of each fidelity data collection month using an online self-administered practitioner and staff version of the “How is UAIHC doing?” questionnaire. Data from audits of randomly selected, de-identified patient charts and of administrative records will also be used to assess indicators of model implementation.

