• Psychological Well-being. Psychological well-being is assessed by the 5-item World Health Organization Well-Being Index (WHO-5) [63]. The WHO-5 assesses subjective quality of life as a dimension separate from social disability and asks about dimensions such as positive mood, vitality, and interest in life in the past 2 weeks.

• Health-related work productivity (absenteeism/presenteeism). Health-related work productivity is assessed by the 6-item Work Productivity and Activity Impairment questionnaire (WPAI) [64]. The WPAI is a self-administered instrument to assess the impact of disease on absenteeism (work time missed), presenteeism (reduced on-the-job effectiveness), and impairment in daily activity.

• Healthcare utilization. Four items based on Ritter et al. (2001) [65] ask about use of healthcare services in the prior period—from primary care providers outside of UAIHC, from specialists, from emergency rooms or urgent care centers, and overnight hospital stays.

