The fifth analysis will focus on the subset of patients for which health insurance claims data are available and will utilize a matched comparison design. Prior to analysis all claims data for each individual (treatment and comparison groups) will be aggregated (by summation) into per health plan member per month (PMPM) totals of paid amounts (the amount paid by the health plan to the practitioner) for each of the following cost categories: total, inpatient, outpatient, emergency room, physician, and pharmaceutical claims. Similarly, the numbers of outpatient visits, hospital stays and emergency department visits will also be aggregated for each individual. The primary outcome will be total cost. Two comparison groups from de-identified claims data will be created—one using simple matching (e.g., by age and gender) and one using propensity scores [49]. After the comparison groups have been selected, simple descriptive analyses will show average PMPM costs and healthcare utilization (including standard deviations and other measures of dispersion) pre- and post- enrollment (or an equivalent date for the comparison groups) by gender, age, baseline diagnosis and by treatment and comparison group. Because cost data tends to be highly skewed, average PMPM costs and healthcare utilization pre/post enrollment, and the change in costs and utilization pre/post between the treatment and each of the comparison groups will be reported as mean differences with confidence intervals calculated using bootstrap methods [83,84]. Because of the number of data points for each patient (e.g., up to 12 PMPM values pre-enrollment and 12 post-enrollment), HLM [80-82] will be used to estimate the pattern of change in healthcare utilization and costs over time, and to explore the determinants of those patterns. Fidelity measures with significant changes over time [24], demographics, participants’ membership level and baseline diagnoses will be included as covariates in these models. Finally, changes in costs between groups will be compared to changes in patients’ CVD risk.

Results for the last two analyses will be reported following the Strengthening the Reporting of Observational Studies in Epidemiology (STROBE) guidelines [85]. For all outcomes, the estimated treatment effects will be reported using their original outcome scale and including confidence intervals.

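### Outpatient visits are counted from insurance claims, but visits covered by the UAIHC membership fee may leave no claim, so UAIHC patients' use after enrollment may be under-counted

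*Protocol article*

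**What the plan says.** The Analysis section of the Protocol article, in the fifth analysis, starts from claims: "Prior to analysis all claims data for each individual (treatment and comparison groups) will be aggregated (by summation") into monthly paid amounts. It then adds that "the numbers of outpatient visits, hospital stays and emergency department visits will also be aggregated for each individual". The results are to be reported as pre/post changes and as differences in change between UAIHC patients and each of two matched groups.

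The Comparison group(s) section confirms the source: "The primary outcome, total healthcare utilization, will be obtained from healthcare claims data for patients whose employers have given access to those data". Data Collection gives the window: "These data will be collected for one year before and one year after clinic enrollment".

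The Intervention section describes hybrid financing, in which insurance reimbursement is supplemented by a membership fee: "The membership fee covers a certain number of CM practitioner visits, health coaching visits, and classes". There are three tiers. The lowest is the "basic bundle (5 visits with the patient’s choice of CM practitioners, 2 visits with a health coach, and 2 groups or classes"); core and expanded double and quadruple those numbers. The section does not say how long a bundle lasts, or whether a fee-covered visit is also submitted to the health plan.

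The self-report utilization items ask about care "from primary care providers outside of UAIHC, from specialists, from emergency rooms or urgent care centers, and overnight hospital stays". None asks about visits at UAIHC.

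**The concern.** A visit count built from claims sees only what was submitted to the plan. If fee-covered visits are not submitted, the count omits part of the care delivered by the clinic under study. The omission is not spread evenly. It can occur only among UAIHC patients and only after they enroll, whereas a visit of the same kind paid by a plan before enrollment, or for a comparison patient, would be counted.

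That is the contrast the fifth analysis reports. Matching on age and gender or on propensity scores does not help, because the problem lies in how the outcome is ascertained, not in who is compared. At stake is whether a fall in the outpatient count may be read as lower use of outpatient services, or only as fewer visits charged to the insurer.

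**Working it through.** **1. Entitlements by tier (Intervention section).**

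| Tier | CM visits | Coach visits | Individual visits | Groups or classes |
|---|---|---|---|---|
| Basic | 5 | 2 | 5 + 2 = 7 | 2 |
| Core | 10 | 4 | 10 + 4 = 14 | 4 |
| Expanded | 20 | 8 | 20 + 8 = 28 | 8 |

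Whether a coaching visit would count as an outpatient visit is not stated, so the CM column is the cautious figure.

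**2. No yearly rate can be derived.** The claims window is 12 months after enrollment, but the bundle period is not given. If a bundle lasted 6, 12 or 24 months (assumed), the individual visits per year for basic, core and expanded would be:
- 6 months: 14, 28 and 56
- 12 months: 7, 14 and 28
- 24 months: 3.5, 7 and 14

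**3. Effect on the count.** Let *k* be the fee-covered visits a member uses in the post-enrollment year that leave no claim, *f* the fall in claim-recorded visits from the pre- to the post-enrollment year, and *c* the change in the matched group.
- Change reported from claims: −*f*. Change in actual use: *k* − *f*.
- Between-group difference reported: −*f* − *c*. Actual: *k* − *f* − *c*.
- Error in both cases: −*k*.

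The pre/post count falls while actual use rises whenever 0 < *f* < *k*. Take *f* = 4 (assumed), all entitled visits used within the year, and none billed. The claims count reports −4 in every case. The actual change is:
- CM visits only: 5 − 4 = +1, 10 − 4 = +6, 20 − 4 = +16
- CM plus coaching: 7 − 4 = +3, 14 − 4 = +10, 28 − 4 = +24

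**4. Dependence on uptake and billing.** With entitlement *E*, uptake *u* and share also billed *b*, *k* = *u*(1 − *b*)*E*. For CM visits alone (*E* = 5, 10, 20), all values of *u* and *b* being assumptions:
- *u* = 1, *b* = 0: *k* = 5, 10, 20
- *u* = 0.5, *b* = 0: *k* = 2.5, 5, 10
- *u* = 0.5, *b* = 0.5: *k* = 1.25, 2.5, 5
- *b* = 1: *k* = 0, and the problem disappears

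**5. Does another listed source recover these visits for the fifth analysis?**
- Self-report items: no item on UAIHC visits.
- Data collected from medical records: laboratory results, vital signs, diagnoses, medication and risk scores; no visit count.
- Patient chart extraction (fidelity): 10 de-identified charts per fidelity month, so it cannot be linked to participants.
- Membership level as a model covariate: an entitlement, not visits used, and without a counterpart in comparison patients.
- Discussion: the limitations mention that usable claims data are hard to obtain, but not this gap.

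None of them does.

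**The case against.** The strongest reply is that the count makes sense from the payer's perspective. Costs are defined as what the plan paid, and visits follow the same basis. Fee-bundled visits are part of the intervention, and whether to call them utilization is partly a choice. That stands as a reading, and it is why relabelling is the first step. The article does not restrict the outcome in this way, however; it speaks of outpatient visits and healthcare utilization in general.

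The absence of a claim is also inferred. Insurance reimbursement supplemented by a fee does not settle how an individual visit is billed. This stands, and the point is conditional on it. So is the remark that a member with no plan-paid CM care before enrollment has no such visits to substitute: for that patient the count misses added use rather than showing a false fall from substitution.

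A condensed article may leave the definition of an outpatient visit to the full protocol. That is fair for the definition, but the article itself fixes claims as the data source, and that choice creates the gap.

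A reader might infer more than the documents support:
- *That the primary outcome is affected.* Comparison group(s) calls utilization primary, and Table 1 marks utilization and costs jointly, but Outcomes sample and Analysis both settle on total cost. Outpatient visits are one of three secondary counts.
- *That 7 to 28 visits a year are lost.* No bundle period and no uptake are given.
- *That the count must mislead.* It does so only to the extent that fee-covered visits are used and not billed.

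**Conclusion.** The concern holds in a limited, conditional form. The stated rule can under-count outpatient visits for UAIHC patients after enrollment and for nobody else. The error in the pre/post and between-group change equals the number of fee-covered visits used without a claim. By entitlement that is up to 5, 10 or 20 CM visits per bundle (7, 14 or 28 with coaching), and it could be zero if all such visits are also billed. The sign of the pre/post change is wrong only when claim-recorded visits fall by less than that number.

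This rests on the inference that at least some fee-covered visits leave no claim, and on uptake that the article does not give. It concerns one secondary count. Hospital stays and emergency visits, counted in the same sentence, are outside what the fee is said to cover, and the valuation of total cost is a separate matter. Within those limits it should be corrected, because it decides whether the study may say that outpatient use fell.

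**What to change.** 1. Name the outcome *insurer-billed outpatient visits* wherever the count comes from claims.
2. State whether fee-covered visits are also submitted to the plan. For participants, extract the number of fee-covered CM visits in the 12 months after enrollment from UAIHC records, leaving out any already present in the claims. Show coaching visits and classes on separate lines.
3. Report the pre/post change and the change against each matched group with and without the fee-covered visits.
4. Do not conclude from the claims count alone that total outpatient use fell.
5. State that self-paid CM visits before enrollment and in comparison patients are unseen. The count with fee-covered visits therefore errs against the clinic and should not be the sole gate for a conclusion; the two versions are to be read together.

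The cost is small: one extra extract of visit counts from a single clinic whose participant charts are already abstracted at 3, 6 and 12 months, plus wording. The claims request, the matching and the hospital and emergency counts stay as they are. What remains is the asymmetry in item 5, which the listed data cannot remove.

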## Discussion

There has been much written about the need for new models of medical care—ones that are more patient-centered, that can empower patients to make positive lifestyle changes, that can lower cost of healthcare, and that offer a sustainable financial model. This study has been designed to test whether an IM primary care practice model (UAIHC) can meet these challenges.

This study will face a number of limitations. For example, some of the self-report measures of fidelity have not been fully tested and validated. The data collection burden on patients might limit enrollment or increase dropout. Also, because this is a new clinic, member enrollment and study adoption rates are unknown and could fall short of predictions. This is especially true for the five targeted conditions; low prevalence will prevent analyses by condition. Obtaining a useable set of claims data is always challenging. Better outcomes (larger effect sizes) may be achieved were factors in the clinic subject to more control (e.g., patient homogeneity, or treatment consistency rather than patient-centered care), or if the clinic had already had time to mature into its final form. Also, at such an early phase of the clinic’s development and management, the methodological rigor required to study this multi-faceted system of care may not be able to yield all of the desired information. Instead, this will be an evaluation of a newly designed and formed IM primary care clinic model in its natural state as it evolves. Some of the data collected during fidelity monitoring will also be useful in improving and optimizing clinic performance. The addition of more qualitative data collection is desirable to more closely examine patient experiences in the clinic and may be possible as funds and time become available.

This protocol is designed to meet the methodological challenges involved in evaluating this complex intervention (IM model of adult primary care) with as much rigor as possible. It is anticipated that its results and the results of anticipated continuous evaluation of the UAIHC will contribute greatly to health services research in integrative medicine.

## Abbreviations

ACES: Ambulatory care experiences survey; CAHPS: Consumer assessment of healthcare providers and systems; CARE: Consultation and relational empathy measure; CER: Comparative effectiveness research; CM: Complementary medicine; CVD: Cardiovascular disease; FIQR: Fibromyalgia impact questionnaire revised; FSS: Fatigue severity scale; fVAS: Fatigue visual analog scale; GAD-2: Generalized anxiety disorder questionnaire ultra-brief 2-item version; GAD-7: Generalized anxiety disorder questionnaire 7-item version; HbA1c: Glycosylated hemoglobin; HLM: Hierarchical linear modeling; IM: Integrative medicine; NAMCS: National ambulatory medical care survey; PAM: Patient activation measure; PHQ-2: Patient health questionnaire ultra-brief 2-item version; PHQ-9: Patient health questionnaire 9-item version; PMPM: Per member per month; PSQI: Pittsburgh sleep quality index; PSS: Perceived stress scale; pVAS: Pain visual analog scale; RCT: Randomized controlled trial; RMDQ: Roland-Morris disability questionnaire; SF-12: 12-Item short form medical outcomes survey; SF-6D: 6-dimentional Health-related quality of life measure based on the short form medical outcomes survey; STROBE: Strengthening the reporting of observational studies in epidemiology guidelines; T4: Total thyroxine; TCI: Team climate inventory; TSH: Thyroid stimulating hormone; UA: University of Arizona; UAIHC: University of Arizona Integrative Health Center; WHO-5: World Health Organization well-being index; WPAI: Work productivity and activity impairment questionnaire.
